## 10.8 Treatment of adverse events

The investigators will provide treatment of adverse events. Advice will be sought from the Local Medical Monitor and other medical specialists as indicated for severe, unusual or complicated medical conditions. Treatment events will be fully documented. Clinical trials insurance will cover medical liability of Malian clinical investigators.

## 10.9 Halting Rules

Because this Phase 1 study is not powered for statistically significant comparisons of adverse event frequencies between groups and because the DSMB will be conducting safety reviews before each dose escalation, statistical halting rules will not be used. Decisions to halt or pause the study will be made by USAMMDA and DMID based on the recommendations of the DSMB. In the event that one or more serious adverse events probably or suspected of being related to vaccination are detected following any immunization in any of the vaccine groups, no further vaccinations will be administered until a written report has been submitted to USAMMDA, DMID, GSKBio, the DSMB, the US Army HSRRB, the University of Maryland IRB, and the FMPOS Ethics Review Committee and the investigators have conferred with the Local Medical Monitor and the DSMB. DMID and USAMMDA retain the authority to halt or pause the study based on recommendations of the DSMB.

However, participants in the first cohort will be divided into half by age. The older half (i.e. the older ten of the 20 children in Cohort 1) will be immunized on one day and the younger half on the next day. To account for possible deferral of immunization due to acute illness or other reasons, at least 80% (8 children) of the older half of Cohort 1 will be immunized before proceeding to immunize any of the younger half of the cohort. No statistical safety evaluation will be performed based on these small subgroups. The intent is to be able to identify any very common, unexpected, severe events that would warrant immediate discussions with DMID, USAMMDA and the DSMB before immunizing the younger participants.

A single vaccine-related SAE in any participant of any cohort at any time within the first seven days of observation (study days 0-7) or a 20% rate of SAEs (related or unrelated) in a cohort during the 7 day surveillance period following immunization will result in a temporary pause in immunizations and consultation with USAMMDA, DMID and the DSMB.

## 10.10 Safety Oversight

### 10.10.1 Local Medical Monitor

A qualified Malian pediatrician will serve as the Local Medical Monitor (LMM) for this study. The LMM's *curriculum vitae* will be maintained on record. She is a qualified and experienced pediatrician not otherwise associated with this protocol, who is able to provide medical care to research subjects for conditions that may arise during the conduct of the study. If safety concerns are identified the LMM may request a meeting of the DSMB to review safety data. The medical monitor is required to review all unanticipated problems involving risk to subjects or others, SAEs, and all subject deaths

associated with the protocol and provide an unbiased written report of the event. For SAEs and deaths she will provide an unbiased written report of the event within 10 calendar days of the initial report. At a minimum, the medical monitor should comment on the outcomes of the event or problem and, in the case of an SAE or death, comment on the relationship to participation in the study. The medical monitor should also indicate whether he/she concurs with the details of the report provided by the study investigator. Reports for events determined by either the investigator or medical monitor to be possibly or definitely related to participation and reports of events resulting in death should be promptly forwarded to the sponsors and the IRBs through the DMID contractor PPDi.

The involvement of the LMM will be particularly important when decisions related to safety of participants have to be made quickly. A copy of treatment codes will be in her safekeeping and she may unblind individual study participants if deemed necessary for medical and/or ethical reasons (for example, in the case of a participant in urgent need of rabies immunization). In exceptional circumstances, for example a death possibly related to vaccination, she would have the authority to temporarily suspend the whole or any specific aspect of the trial pending review by the USAMMDA and DMID Medical Monitors and the DSMB.

The LMM will be on-site during active phases of immunization and during the immediate post-vaccination surveillance period. A physician on staff at the Bandiagara Health Center who resides full time in Bandiagara will act as the on-site LMM in support of the LMM between the vaccinations.

The LMM's role will include:

- Acting as the study participants' advocate
- Providing advice to the investigators on whether a set of clinical circumstances in a study warrants formal notification to the DMID and USAMMDA Medical Monitors and the DSMB.
- Providing clinical advice on any illness in study subjects especially in circumstances in which treatment might influence the course of the trial.
- Review all SAEs as outlined above

The LMM will liaise closely with the PI throughout the course of the trial and relay relevant safety information to the PI. The PI and co-PI will subsequently inform the FMPOS IRB, the DSMB, DMID, GSKBio, WRAIR, USAMMDA and USAID of safety concerns that arise.

## **10.11 Data Safety and Monitoring Board (DSMB)**

An independent DSMB will be constituted by DMID to review safety data at specified intervals prior to each dose escalation. The role of the DSMB is to provide safety oversight over the conduct of the trial. It will review blinded safety data before each dose escalation and advise on progression to the next dose level. The DSMB will hold two conference calls to review the safety data generated from the trial up to that point. These calls will occur as soon as possible after the completion of the 7-day

surveillance period following each of the first 2 immunizations of cohorts 1 and 2. The first call will thus occur approximately one week before the first immunization with the 25 µg dose level of FMP2.1, and the second will occur approximately one week before the first immunization with the 50 µg dose level (Figure). The purpose of these conference calls will be to review the accumulated safety data to advise whether or not the study can proceed with the dose escalation, and whether the trial can proceed generally. In the event that the DSMB identifies a safety concern, the collaborative group including the investigators, DMID, WRAIR, GSK and USAID will review all safety data to decide whether to give the next sequential dose. Senior investigators and representatives from USAMMDA, DMID, WRAIR, GSK and USAID will be invited to but not obligated to participate in the conference calls during open sessions, which will be followed by closed sessions including only DSMB members.

[figure not shown]

**Figure.** Timeline for safety reviews by DSMB. Arrows down indicate immunization safety data included in safety review. Arrows up indicate review results in recommendation to proceed with immunization.

The DSMB will meet after the 7-day surveillance period following the last immunization of cohort 3 to review safety data and provide advice to the sponsors and investigators with regard to dose selection for the subsequent Phase 2 trial.

The investigator will inform the DSMB of:

- All subsequent protocol amendments, informed consent form changes or revisions of other documents originally submitted for review
- Serious adverse events (SAEs), grade 3 adverse experiences and grade 2 abnormalities of laboratory tests occurring during the study, regardless of relationship to the study vaccine
- New information that may affect adversely the safety of the subjects or the conduct of the study.

The DSMB may recommend that the Sponsor, USAMMDA, in conjunction with DMID, put the study vaccinations on temporary hold pending review of potential safety issues. The DSMB will request

additional information from the Principal Investigator as needed and will request any appropriate statistical calculations to support discussions with the Sponsor, USAMMDA, in conjunction with DMID. All documentation provided to members of the DSMB for information and review will be treated in a confidential manner.

## **11 CLINICAL MONITORING**

### **11.1 Site Monitoring Plan**

Site monitoring will be conducted by DMID or its designated monitoring contractor, to ensure that GCP standards and regulatory guidelines are being followed. Pre-trial monitoring visits will be made to the site, including the clinical laboratory. All records will be made available to monitors, including regulatory files, CRFs and other source documents, QA/QC documentation, SOPs, etc. At the discretion of the monitor, additional site visits may be made during the course of the trial and at the end of the surveillance period.

In addition, monitors from USAMMDA and GSKBio may make site visits, in coordination with the primary monitoring group designated by DMID. DMID or its designated monitoring contractor and monitors from USAMMDA and GSKBio should coordinate their visits in order to reduce the burdens to the clinical study site, clinical investigation staff and study participants.

In conjunction with the monitoring body designated by DMID, a detailed monitoring plan, subject to approval by OCRA, will be developed and included in the Manual of Procedures. The monitoring plan will include the number of subject charts to be reviewed, which/what proportion of data fields and what will be monitored, and who will be responsible for conducting the monitoring visits, and who will be responsible for ensuring that monitoring findings are addressed.

## 12 STATISTICAL CONSIDERATIONS

Data entry will be performed on site and in the MRTC/MMVDU data management unit in Bamako if necessary. The EMMES Corporation will do data analysis and reporting for primary and secondary endpoints in collaboration with the MRTC Data Management Unit.

### 12.1 Primary endpoints

- Occurrence of solicited symptoms during a 7-day surveillance period after vaccination (day of vaccination and study days 1, 2, 3 and 7).
- Occurrence of unsolicited symptoms during a 30-day surveillance period after vaccination.
- Occurrence of serious adverse events during the study period.

### 12.2 Secondary endpoints

- Titers and activity of anti-FMP2.1 antibody at each time point where serology samples are analyzed, measured by ELISA\*, by process inhibition assay and growth inhibition assay, (in this order of priority when serum quantities are limited).
- Cellular immune responses at each time point
- Incidence of unique haplotypes of AMA-1 domain I in *P. falciparum* infections detected during follow-up

\*The antibody response to FMP2.1 by ELISA will be the main measure of immunogenicity for consideration in dose selection for efficacy trials.

### 12.3 Study cohorts/datasets to be evaluated

#### Total cohort

The 'Total Cohort' will include all participants enrolled (defined as randomized to study groups) in the study.

#### Safety cohort

The 'Safety Cohort' will consist of all participants who have received at least one dose of study vaccine or comparator and for whom any data on safety are available.

The presentation of safety data will explore separately the adverse experiences among participants who received all vaccinations, among those who received only some and among those with clinical violations of study protocol.

### Immunogenicity cohort

The 'Immunogenicity Cohort' will include all evaluable participants (i.e., those meeting all eligibility criteria, and who have received at least one immunization with any of the study or control vaccines) for whom data concerning immunogenicity endpoint measures are available. This will include participants for whom assay results are available for antibodies against at least one study vaccine antigen component after vaccination.

## 12.4 Sample Size Considerations

The sample size is driven by the primary endpoint, safety. However, this Phase 1 trial is not powered to detect differences between groups. Even if comparative statistics for the safety variables are computed, the study will have low power to detect anything other than very large differences in the incidence of local and general side effects between the vaccination groups. This is done weighing the need to detect any possible untoward reactions against the need to limit the number of participants involved for safety purposes. The sample size of 30 in each study group is widely accepted and used in industry for the initial assessment of the safety, tolerance and immunogenicity of an investigational vaccine, including other blood-stage subunit protein malaria vaccines with the AS02A and other adjuvants. Incorporation of a comparator vaccine as control will enable broad initial estimates of the incidence of local and general side effects and of immune responses among vaccine recipients. Table 12 provides the probability of detecting events in the groups of 30 that will receive the 25 µg and 50 µg doses. For example, if the "true" rate of an SAE is 5%, then the probability of observing no events (Pr 0/30) in a group size of 30 is 0.21 and the probability of observing one or more events (Pr 1+/30) in a group size of 30 is 0.79.

Table 12. Event detection probability table.

| Event Rate | Pr 0/30 | Pr 1+/30 |
|------------|---------|----------|
| 0.01       | 0.74    | 0.26     |
| 0.05       | 0.21    | 0.79     |
| 0.08       | 0.08    | 0.92     |
| 0.10       | 0.04    | 0.96     |

Event rate. True rate at which an event occurs.

Pr 0/30. Given the event rate, probability that no events will be detected among 30 vaccinees.

Pr 1+/30. Given the event rate, probability that one or more events will be detected among 30 vaccinees.

The inclusion of an initial group of 20 children randomized 3:1 to receive 10 µg of FMP2.1 in 0.1 mL of AS02A or control vaccine is for the purpose of assuring that there is not a common adverse reaction in children that should preclude further testing. This is not considered a dose level to be evaluated for further clinical development and thus does not warrant the larger sample size of the 25 µg and 50 µg dose level groups.

## **12.5 Final Analysis Plan**

A final research analysis plan will be agreed upon by the investigators, USAMMDA, DMID, WRAIR, GSKBio and USAID prior to locking of the database for the final analysis. This plan will include information on adverse events by dose and number of vaccinations. The primary analysis will be conducted on data and samples collected until Day 90 (30 days post Immunization 3 for each cohort). The primary analysis will be used for decision-making related to the product clinical development plan. The study will continue in a single blind manner for additional safety surveillance and immunogenicity assessment. This additional information will be appended to the study report. It is anticipated that the results of this study will be presented to the scientific community via oral presentations at meetings and written publications in scientific journals. The data to be presented and the authorship will be discussed between partners prior to any official communication.

The official report of the primary analysis will be written by the study investigators and the statistical consultant and submitted through appropriate channels and upon approval by USAMMDA and DMID. This report will contain detailed information about the participants, their tolerance of the vaccines, their side effects and laboratory abnormalities, as well as their overall immune responses to immunization.

### **12.5.1 Analysis of demographics**

Demographic characteristics (age, sex, and place of residence) of each study cohort will be tabulated. The mean age (plus range and standard deviation) by sex of the enrolled participants, as a whole and per group will be tabulated.

### **12.5.2 Analysis of immunogenicity**

The primary immunogenicity endpoint of ELISA titers of FMP2.1 antibodies will be assessed in several ways. A series of graphs will display immunologic responses. For each vaccine group and time point, the distribution of anti-FMP2.1 antibody levels and reverse cumulative distribution curves will be plotted. Corresponding summary statistics will show means and standard deviations as well as median, 25th and 75th percentiles, and 10th and 90th percentiles. The results will be presented both as raw data and as log-transformed data.

In addition, for each treatment group and time point, anti-FMP2.1 antibody levels will be presented as geometric means of OD units with 95% confidence intervals. For each vaccine group and for each time point, a table will show the proportion of participants with two-fold, four-fold, and eight-fold increases in anti-FMP2.1 antibody titers relative to their pre-immunization titers.

### **12.5.3 Analysis of safety**

The overall percentage of participants with at least one local adverse event (solicited or unsolicited) and the percentage with at least one general adverse event (solicited and unsolicited) during the 7-day surveillance period after vaccination will be tabulated. The incidence, intensity and relationship of individual solicited symptoms over the 7-day surveillance period will be calculated per group and vaccine administration.

The number of participants with at least one report of an unsolicited adverse event, classified by WHO-preferred terms, reported up to 30 days after vaccination will be tabulated per group and vaccine administration. The intensity and relationship to vaccination of the unsolicited symptoms reported will also be assessed.

Serious adverse events are expected to be rare, but where observed will be described. Comparisons between study groups of incidence of symptoms, local and general symptoms will be made based on a two-sided Fisher's Exact Tests. Analysis of safety during the 15-month surveillance period will consist of comparison of incidence of serious adverse events as well as hemoglobin, creatinine and ALT levels.

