#### 2.4.6 Summary of clinical experience with AMA-1 FMP2.1/AS02A

On the basis of preclinical and clinical studies performed to date with FMP2.1/AS02A, there are no risks of particular severity or seriousness anticipated with the formulation.

Although the two previous clinical studies with FMP2.1/AS02A have resulted in grade 3 reactions; these reactions were generally short-lived and resolved in less than 48 hours after vaccination. In malaria-exposed Malian adults followed for a year, there were more unsolicited adverse events, as expected. Malian adults also experienced more local injection site swelling, which was short-lived and usually not symptomatic. This raises the possibility that the vaccine is more reactogenic in malaria-exposed than in malaria-naïve individuals and justifies the careful dose escalation proposed in this protocol.

Extensive clinical data exist for AS02A administered with FMP2.1, additional malarial antigens, hepatitis B surface antigen (HBsAg), and HIV antigens. Clinical development with these vaccines is ongoing. In general the AS02A formulated vaccines are safe and well tolerated when administered to adults, both naïve and malaria experienced, and in malaria experienced children. The most common side effect related to immunization is pain at the injection site. Redness and swelling are less frequent. The most frequent general side effects are headache and malaise, usually mild to moderate and short in duration. Various studies have shown that AS02A formulated vaccines are safe and well tolerated and the reactogenicity profile was clinically acceptable. Based on the experience with the FMP2.1 antigen and the AS02A adjuvant, other than standard precautions for idiosyncratic or allergic reactions, a need for special monitoring is not anticipated in the present trial.

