### **3.2 Study Outcome Measures**

#### **3.2.1 Primary Outcome Measures**

1. Occurrence of solicited symptoms after each vaccination during a 7-day surveillance period (day of vaccination and days 1, 2, 3 and 7 after vaccination)
2. Occurrence of unsolicited symptoms after each vaccination during a 30-day surveillance period (day of vaccination and 30 subsequent days)
3. Occurrence of serious adverse events throughout the study period

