### **10.2 Methods and Timing for Assessing, Recording, and Analyzing Safety Parameters**

#### **10.2.1 Adverse Events**

An adverse event includes any noxious, pathological or unintended change in anatomical, physiological or metabolic functions as indicated by physical signs, symptoms and/or laboratory detected changes occurring in any phase of the clinical study whether associated with the study vaccine or active comparator vaccine and whether or not considered vaccination related. This definition includes an exacerbation of pre-existing conditions or events, intercurrent illnesses, or vaccine or drug interaction. Symptomatic uncomplicated or severe malaria infection will be coded as adverse events as will any other acute illness, throughout the 15 months of the study. Anticipated day-to-day fluctuations of pre-existing conditions that do not represent a clinically significant exacerbation need not be considered adverse events. Discrete episodes of chronic conditions occurring during a study period will be reported as adverse events to assess changes in frequency or severity.

Adverse events will be documented in terms of a medical diagnosis. When it is not possible to make a specific medical diagnosis, the adverse event will be documented in terms of signs and/or symptoms observed by the investigator or reported by the subject at each study visit. Pre-existing conditions or signs and/or symptoms (including any that are not recognized at study entry but are recognized during the study period) present in a participant prior to the start of the study will be recorded on the participant's CRF. Any hospitalization will be considered a serious adverse event. Adverse events to be recorded as endpoints are described below. All other adverse events will be recorded as unsolicited adverse events.

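### The only overall local and general adverse event percentages in section 12.5.3 pool solicited with unsolicited events, so they match neither of the first two primary endpoints

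*Protocol*

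**What the plan says.** Section 3.2.1 gives the first primary outcome as "Occurrence of solicited symptoms after each vaccination during a 7-day surveillance period", and sections 10.1 and 12.1 repeat it. The second primary outcome is unsolicited symptoms over 30 days.

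Section 12.5.3 then sets out the safety analysis:

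- For general events, "the percentage with at least one general adverse event (solicited and unsolicited) during the 7-day surveillance period after vaccination will be tabulated". The overall local percentage also pools solicited and unsolicited events. Neither is restricted to events judged related.
- For single symptoms, "The incidence, intensity and relationship of individual solicited symptoms over the 7-day surveillance period will be calculated per group and vaccine administration".
- Unsolicited events up to 30 days have their own table, with intensity and relationship.
- For testing, "Comparisons between study groups of incidence of symptoms, local and general symptoms will be made based on a two-sided Fisher's Exact Tests".

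Section 10.2.1 sets what can enter the pooled figure: "Symptomatic uncomplicated or severe malaria infection will be coded as adverse events as will any other acute illness". Section 10.2.5 makes any event outside the solicited list unsolicited. Section 12.4 says that the trial is not powered for comparisons between groups.

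**The concern.** A reactogenicity summary should count, per child, whether any of the listed reactions occurred after vaccination. The overall percentages in section 12.5.3 also count every other event in the same week, related or not. They are too broad for endpoint 1 and cover too short a window for endpoint 2.

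In this population much of the added part is likely to be intercurrent illness. Section 2.2.1 reports an average of 1.92 clinical malaria episodes per child per season. Section 2.4.6 says of the earlier adult trial at this site: "In malaria-exposed Malian adults followed for a year, there were more unsolicited adverse events, as expected". If such illness is equally frequent in all arms, it raises every arm's percentage and narrows the difference between arms. The general percentage is the more exposed of the two, since intercurrent illness seldom produces an injection-site event.

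The trial is meant to support a choice of dose with acceptable reactogenicity (section 3.1.1). A per-child summary that understates a difference in systemic reactions would serve that purpose less well than one built on solicited events.

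**Working it through.** **The plan's own figure.** The only sample-size calculation is the event-detection table in section 12.4. Pr(at least one event in 30) = 1 − (1 − p)^30 gives 0.260, 0.785, 0.918 and 0.958 for p = 0.01, 0.05, 0.08 and 0.10. The stated 0.26, 0.79, 0.92 and 0.96 reproduce. The table does not address the composite.

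**Direction of the effect.** Let p be the probability of at least one solicited general event, and u the probability of at least one independent background event, equal in both arms. The pooled probability is 1 − (1 − p)(1 − u), so the risk difference is multiplied by (1 − u). It can only shrink.

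**Inputs for the size.**

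- Solicited general events in the Malian adult trial, from Table 7 (headache, fever, malaise, myalgia, arthralgia, chills, nausea; all grades):
  - 50 µg: 18 + 6 + 5 + 7 + 2 + 2 + 1 = 41 in 59 doses (Table 1), or 0.695 per dose.
  - Rabies: 10 + 1 + 3 + 3 + 3 + 1 + 1 = 22. Assuming 60 doses, this is 0.367 per dose.
- Background malaria in children: 1.92 episodes per July–December season (section 2.2.1), so 1.92/26 weeks ≈ 0.074 per 7-day window, and u = 1 − exp(−0.074) ≈ 0.07.
- Group sizes: 30 in the 50 µg group and 25 pooled rabies recipients. A two-sided 0.05 level is assumed, because none is stated.

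**Formula.** Treating events as independent (Poisson), P(at least one over k doses) = 1 − exp(−k × (solicited rate + background rate)). Power is that of the exact two-sided Fisher test, by enumeration.

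| Measure, 50 µg v rabies | Per dose | Difference | Over three doses | Fisher power, three doses |
|---|---|---|---|---|
| Solicited only | 50.1% v 30.7% | 19.4 points | 87.6% v 66.7% | 39% |
| Plus in-season malaria (0.074 per week) | 53.6% v 35.6% | 18.0 points | 90.0% v 73.3% | 29% |

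Per-dose power is about 25% for solicited only and 21% with malaria added.

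**Larger backgrounds, as a sensitivity range only.** A background of 0.5 per week, which has no source in the protocol, gives 70% v 58% per dose (12 points) and three-dose power of about 5%. A background of 1.6 per week gives 90% v 86% (4 points) and power of about 0%. The 1.6 is an adult figure. For rabies, Table 6 (all events) minus Table 7 (solicited) is 151 − 55 = 96 events in an assumed 60 doses. The same subtraction gives 229 − 118 = 111 in 60 doses at 25 µg and 238 − 134 = 104 in 59 doses at 50 µg. These are event counts, not counts of affected children.

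**Sensitivity to clustering.** If each affected dose carried two symptoms, the solicited-only contrast would be 1 − exp(−0.695/2) v 1 − exp(−0.367/2), about 29% v 17% (13 points). Adding malaria gives 34% v 23% (12 points).

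**The case against.** The strongest reply is that endpoint 1 is analysed free of unsolicited events. Section 12.5.3 takes each solicited symptom by group and by dose, with intensity and relationship, directly after the pooled percentages. This stands. A reader might infer that pooling dilutes the vaccine effect on endpoint 1 itself, and the text does not support that. Only the overall summaries are affected.

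A reader might also infer that the pooled figure is the headline measure for choosing between 25 and 50 µg, or that it is what the Fisher test compares. No section calls it the headline or ties dose selection to it; section 2.4.8 refers to safety, reactogenicity and immunogenicity in general. The Fisher sentence speaks of local and general symptoms and does not say whether these are the pooled percentages, solicited classes or individual symptoms. That is an ambiguity, not a stated choice.

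The size is open to challenge too:

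- Headache, malaise, myalgia, arthralgia, chills and nausea, which supply most of the adult rates, are not on the children's list in section 10.2.4.
- Symptoms cluster within a person.
- Section 9.3.3 leaves open when immunization falls relative to the transmission season.
- Some malaria will present as fever, a solicited symptom, so a solicited-only percentage would still carry some background.

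All of this stands, and it limits the claim to a modest loss. Section 12.4 also disclaims comparative power, so a failed powered test is not the harm.

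Finally, a solicited-only row could be left to the later analysis plan that section 12.5 announces. That answers only part of the point. The protocol does not leave the overall measure open; it fixes one, on an event set that matches neither endpoint. Several sparse single-symptom tables do not replace one per-child solicited summary.

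**Conclusion.** The point holds in limited form. The overall local and general percentages in section 12.5.3 pool solicited and unsolicited events over 7 days regardless of relatedness, and so correspond to neither endpoint 1 nor endpoint 2. This mismatch follows from the text alone and depends on no assumed rate.

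Background illness attenuates the pooled figures. With the one paediatric illness rate that the protocol gives, in-season malaria, the loss is small: about 19 to 18 points per dose, and about 39% to 29% in three-dose Fisher power. These figures assume that adult solicited rates apply to children, that events are independent, that background is equal across arms, that rabies recipients had 60 doses in the adult trial, and that vaccination falls in season. A near-total loss of contrast appears only with illness rates that the protocol does not document for children. The consequence is a blurred reactogenicity summary, not a compromised primary endpoint.

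**What to change.** In section 12.5.3:

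1. Add the percentage of children with at least one solicited local and at least one solicited general adverse event, any grade and Grade 3, per group, for each dose and over all doses.
2. State that the Fisher comparison of local and general symptoms uses these percentages.
3. Keep the pooled any-adverse-event percentage as supportive.
4. Report unsolicited events in the same 7 days on a separate line, all and judged related.

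The cost is a wording change. Solicited and unsolicited events are already recorded on separate CRF pages with intensity and relationship (section 10.2.3), so no new data are needed.
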